## Abstract

**Background:**

Provoked vestibulodynia is the most common form of vulvodynia. Despite its high prevalence and deleterious sexual, conjugal, and psychological repercussions, effective evidence-based interventions for provoked vestibulodynia remain limited. For a high proportion of women, significant pain persists despite the currently available treatments. Growing evidence suggests that the central nervous system (CNS) could play a key role in provoked vestibulodynia; thus, treatment targeting the CNS, rather than localized dysfunctions, may be beneficial for women suffering from provoked vestibulodynia. In this study, we aim to build on the promising results of a previous case report and evaluate whether transcranial direct-current stimulation, a non-invasive brain stimulation technique targeting the CNS, could be an effective treatment option for women with provoked vestibulodynia.

**Methods/design:**

This single-center, triple-blind, parallel group, randomized, controlled trial aims to compare the efficacy of transcranial direct-current stimulation with sham transcranial direct-current stimulation in women with provoked vestibulodynia. Forty women diagnosed with provoked vestibulodynia by a gynecologist, following a standardized treatment protocol, are randomized to either active transcranial direct-current stimulation treatment for ten sessions of 20 minutes at an intensity of 2 mA or sham transcranial direct-current stimulation over a 2-week period. Outcome measures are collected at baseline, 2 weeks after treatment and at 3-month follow-up. The primary outcome is pain during intercourse, assessed with a numerical rating scale. Secondary measurements focus on the sexual function, vestibular pain sensitivity, psychological distress, treatment satisfaction, and the patient’s global impression of change.

**Discussion:**

To our knowledge, this study is the first randomized controlled trial to examine the efficacy of transcranial direct-current stimulation in women with provoked vestibulodynia. Findings from this trial are expected to provide significant information about a promising intervention targeting the centralization of pain in women with provoked vestibulodynia.

**Trial registration:**

Clinicaltrials.gov, NCT02543593. Registered on September 4, 2015.

**Electronic supplementary material:**

The online version of this article (doi:10.1186/s13063-016-1366-5) contains supplementary material, which is available to authorized users.

## Background

Chronic vulvar pain represents a major health concern for women. Vulvodynia is a highly neglected chronic pain condition, affecting nearly 10 % of the female population [1]. Suspected to be the foremost cause of pre-menopausal vulvodynia, provoked vestibulodynia (PVD) is characterized by an acute recurrent pain located at the vulvar vestibule (i.e., the vaginal entrance) in response to pressure application or attempted vaginal penetration [2]. It has been revealed that PVD disrupts personal lives, severely affects sexual function, and negatively impacts the quality of life [3, 4]. PVD has also been related to relationship problems and psychological distress [5]. Poorly understood and often misdiagnosed or ignored, PVD pain leads to a high personal cost for patients and substantial financial cost for society. Women with PVD often multiply their medical visits hoping to find relief and rely mainly on non-evidence-based, ineffective interventions [6].

Many empirical treatment options are proposed to women with PVD. Firstly, localized interventions such as topical lidocaine application [7], pelvic floor physical therapy [8], biofeedback technique [9], Botox® injection [10], topical use of estradiol and testosterone compounds [11], and vestibulectomy (surgery) [12] can be offered. As a second option, psychotherapeutic interventions can be proposed, which include cognitive behavioral therapy (CBT) focusing on reducing pain and improving sexual function [13]; hypnotherapy [14]; or acupuncture [15]. In addition, the use of systemic treatments, such as tricyclic antidepressants [16], anticonvulsant medication and selective serotonin reuptake inhibitors (SSRIs) [17], can also be prescribed. Despite this wide variety of treatment options, a high proportion of women with PVD are refractory to conventional treatments [12, 17, 18], highlighting the need for novel approaches.

Recently, alterations in central pain mechanisms have been suggested to play a key role in PVD, potentially explaining the limited success obtained in some patients, with treatments targeting the pain locally in the area of the vestibule. Central sensitization has been observed in many chronic pain conditions, including chronic pelvic pain [19]. While the heightened sensitivity of peripheral pain receptors following local trauma or infection usually resolves with time, in chronic pain, this hypersensitivity is sustained and amplified by an extensive central neural network that includes the spinal dorsal horn, limbic system, and cortical structures [20]. Recent studies suggest that the pathophysiology of PVD is not only limited to the vulvar vestibule but also involves central pain processing alterations similarly to other chronic pain conditions [21]. In support of such central alterations, women with PVD have been shown to be more sensitive in areas other than the genital regions compared to controls (lower pain threshold) [21–23]. Moreover, imaging studies have revealed increased activation of brain regions associated with pain perception during painful stimuli in women with PVD [24], a pattern of results analogous to that observed in studies completed in other chronic pain populations such as fibromyalgia [25–27], irritable bowel syndrome [28–33], and idiopathic back pain [34].

Imaging studies have also shown structural changes in women suffering from PVD. Schweinhardt et al. [35] revealed higher gray matter densities in pain modulatory and stress-related areas in women with PVD, suggesting potential alterations in the supraspinal pain modulatory circuitry. These neuroanatomical changes in CNS regions related to endogenous pain modulation could explain the large-scale changes in pain sensitivity observed in women with PVD (e.g., lower pain thresholds in regions other than the vulvar vestibule). Another argument in favor of central pain mechanism alterations is the co-occurrence of other pain conditions such as orofacial pain, fibromyalgia, and irritable bowel syndrome [4, 36]. Arnold et al. [4] found that women with vulvar pain have a threefold to fourfold risk of having these concomitant pain conditions. Furthermore, similar medications (e.g., antidepressants) are commonly used to treat PVD, fibromyalgia, and irritable bowel syndrome, suggesting that these disorders may share similar pathophysiological mechanisms [37–39].

One proposed technique for modulating CNS activity in chronic pain states is noninvasive brain stimulation (NIBS). NIBS strategies aimed at modifying cortical excitability for different purposes have emerged in recent years [40]. Transcranial direct-current stimulation (tDCS) is a specific form of NIBS that has been shown effective for improving various chronic pain conditions relating to spinal cord injury [41], fibromyalgia [42], multiple sclerosis [43], painful diabetic polyneuropathy [44], pelvic pain [20, 45], and other various syndromes such as trigeminal neuralgia, post-stroke pain syndrome, and back pain [46]. tDCS is a painless technique that consists of applying a low direct current through electrodes placed on the scalp to target the cerebral cortex in order to modify cortical excitability and reduce pain [40]. tDCS is a safe and simple device and could be easily integrated into a rehabilitation program.

Even if a large literature concerning tDCS in pain relief now exists [40, 47, 48], to our knowledge, only one case looking into the effect of tDCS in women with vulvodynia [49] exists. In this case report, Cecilio et al. describe the case of a woman suffering from severe chronic vulvar pain refractory to many empirical treatments (tricyclic antidepressants, anticonvulsants, and opioid analgesics) who has experienced remarkable long-lasting pain relief with tDCS. On the basis of the pathophysiology of chronic pain related to PVD that is similar to other chronic pain syndromes, and considering that it is a neglected women’s health condition, we believe it is important to study the efficacy of this promising treatment in women with PVD. The main goal of this study is to evaluate the efficacy of active tDCS treatment in women with PVD compared to sham tDCS for pain during intercourse, as assessed with a numerical rating scale. We expect that active tDCS treatment will significantly reduce pain during intercourse (2-week post-treatment and 3-month follow-up compared to the pretreatment assessment). We expect that active tDCS treatment will be more effective for reducing pain than the sham tDCS treatment at 2-week post-treatment and 3-month follow-up.

Secondary objectives are to compare the efficacy of active tDCS vs. sham tDCS on sexual function, sexual satisfaction, vestibular pressure-pain threshold, psychological distress (catastrophizing, anxiety, depression, fear of pain, and vaginal penetration cognition), treatment satisfaction, and patient global impression of change (2-week post-treatment and 3-month follow-up compared to pretreatment assessment).

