- Experience moderate to severe pain (minimum of 5/10 on a numerical rating scale (NRS)) in at least 90 % of attempted sexual intercourse - Pain limited to the vestibule during vaginal intercourse and during activities exerting pressure on the vestibule (tampon insertion, tight jeans or pants, cycling, horseback riding) - Presence of provoked vestibulodynia (PVD) for at least 6 months and diagnosed according to the standardized gynecological examination protocol by one of our staff gynecologists - Have a stable sexual partner (sexual activity should include some attempted vaginal penetrations in order to evaluate pain intensity)	- Urogynecological conditions (e.g., active urinary tract or vaginal infection or in the last 3 months, etc.) and other pelvic pathology associated with pelvic pain (e.g., deep dyspareunia) - Have given birth in the last year and breast feeding - Anterior vulvar or vaginal surgery - Refusal to refrain from other treatments 1 month prior to first treatment study until the last 3-month follow-up assessment - Contraindications to transcranial direct-current stimulation (tDCS) (e.g., metallic implant in or near the skull, history of epilepsy, pacemaker) - Previously received tDCS treatment

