#### Primary outcome measure

As recommended by the IMMPACT [67, 68], participants are asked to evaluate their pain during intercourse with an NRS, 0 indicating no pain, and 10, the worst pain ever experienced. This scale has been frequently used in women with PVD [13, 69–71] and shows good reliability, validity, and responsiveness to change [13, 52, 69–71].

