#### Statistical analyses

Baseline characteristics of the sample will be presented using descriptive statistics. Analyses will be done on the intention-to-treat basis. Parametric test assumptions will be examined and reported. If the data is not normally distributed, nonparametric data will be transformed. The effects of treatment on pain, sexual function and psychological distress will be examined using a mixed linear model for repeated measures. One of the factors will be the GROUP, at two levels (the treatment group receives active tDCS, and the control group, sham tDCS), while the repeated factor will be TIME (baseline, 2-week post-treatment, and 3-month follow-up assessments). Treatment efficacy will be judged on the basis of a significant GROUP*TIME interaction and contrast analysis (i.e., Tukey-Kramer contrasts when using a mixed-model approach) [101] to detect any differences. The difference between the two groups regarding satisfaction and PGIC will also be assessed using a mixed linear model for repeated measures. However, the baseline assessment will not be a repeated time-factor for these analyses. All statistical analyses will be conducted at a level of significance of 0.05. Sensitivity analyses will be conducted to explore the effect of multiple imputation methods to replace missing data. The non-robustness of our results due to missing value will be noted and discussed.

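### One of the two stated hypotheses on the primary outcome is a within-arm fall from baseline, which could be reported as confirmed even if active and sham tDCS fall equally

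*Protocol article*

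**What the plan says.** All references are to the protocol article.

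- **Background, aim:** "The main goal of this study is to evaluate the efficacy of active tDCS treatment in women with PVD compared to sham tDCS for pain". This is a between-arm aim, for intercourse pain.
- **Background, first expectation:** "We expect that active tDCS treatment will significantly reduce pain during intercourse (2-week post-treatment and 3-month follow-up compared to the pretreatment assessment". It predicts significance, and its only reference is the woman's own baseline.
- **Background, second expectation:** "We expect that active tDCS treatment will be more effective for reducing pain than the sham tDCS treatment at 2-week post-treatment and 3-month follow-up".
- **Participants, Table 1:** entry requires "Experience moderate to severe pain (minimum of 5/10 on a numerical rating scale (NRS)) in at least 90 % of attempted sexual intercourse", and also "Presence of provoked vestibulodynia (PVD) for at least 6 months".
- **Primary outcome measure:** the outcome is self-reported on the same kind of scale: "participants are asked to evaluate their pain during intercourse with an NRS, 0 indicating no pain, and 10, the worst pain ever experienced".
- **Sample size, power, and statistical analysis methods:** 34 women in total, from an unpaired t test for a difference of 2 points with SD 2.0. Forty are recruited to allow for dropout.
- **Statistical analyses:** "Treatment efficacy will be judged on the basis of a significant GROUP*TIME interaction and contrast analysis". The contrasts are Tukey-Kramer and are meant to pick up differences in general; the section does not say which of them bear on efficacy. "All statistical analyses will be conducted at a level of significance of 0.05".

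**The concern.** Only the second expectation uses the randomised sham control. The first is a pre-post comparison in one arm. Women in that arm attend ten sessions of a credible procedure, rate their own pain, and were admitted because their pain on an NRS was high. Any fall from these sources occurs in the active arm whether or not the current does anything, which is why the trial has a sham arm.

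What is at stake is the conclusion that may be drawn. If both arms fell by the same amount, the interaction would be null. A report could still say, as predicted, that active tDCS significantly reduced pain during intercourse. The analysis section leaves room for this: Tukey-Kramer is an all-pairs method, and the pairs include active follow-up versus active baseline.

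There is a second cost. A family that includes within-arm pairs spends the error rate on comparisons that cannot show efficacy, and takes power from the active-versus-sham comparison for which the trial was sized.

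**Working it through.** **1. The plan's own figure.** Difference 2, SD 2.0, two-sided α 0.05 (sidedness is not stated; assumed), power 0.80 (printed as β). The two-sample t test gives 16.7, so 17 per arm and 34 in total, with power 0.807 at 17 per arm. Allowing 15% dropout, 34 / 0.85 = 40. The figure reproduces, and it rests on the between-arm comparison.

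**2. Chance of a significant within-arm fall when tDCS has no effect.**

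Inputs from the document: SD 2.0 (applied at each visit), n = 17 per arm. Assumed, because the document gives neither: a correlation r between visits and a non-specific fall m.

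- SD of change = 2√(2(1 − r)). At r = 0.5 this is 2√1 = 2.0; at r = 0.3, 2.37; at r = 0.7, 1.55.
- Noncentrality = m√17 / SD of change. At r = 0.5 and m = 1.0: 4.123 / 2.0 = 2.06.
- Unadjusted paired t test: 16 df, critical value 2.12.
- Tukey adjustment over six group-by-time cells: critical value 2.94 at 64 df.

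Probability of a significant fall at one follow-up visit:

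| Non-specific fall | r = 0.3, unadjusted | r = 0.5, unadjusted | r = 0.7, unadjusted | r = 0.5, Tukey |
|---|---|---|---|---|
| 0.5 | 0.13 | 0.16 | 0.24 | 0.03 |
| 1.0 | 0.37 | 0.49 | 0.71 | 0.20 |
| 1.5 | 0.69 | 0.83 | 0.96 | 0.56 |
| 2.0 | 0.91 | 0.97 | about 1.00 | 0.88 |

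With all 20 women per arm and r = 0.5, the unadjusted values are 0.19, 0.56, 0.89 and 0.99.

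These are probabilities of detecting a real but non-specific fall. They are not type I error rates of the pre-post test, whose null hypothesis is no change.

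**3. The damaging pattern.** Simulating equal falls in both arms at r = 0.5, the active-arm fall is significant while the between-arm difference in change is not in about 46%, 80% and 93% of trials, for falls of 1.0, 1.5 and 2.0 points.

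**4. The formal efficacy rule in the same scenario.** With three visits and 17 per arm, the GROUP*TIME interaction is significant in about 5% of trials. Interaction and unadjusted active-arm pre-post test are both significant in about 2.5% to 4.4% of trials at r = 0.5, and in about 3% to 5% at r = 0.7. The rule as written therefore holds its error rate.

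**5. Regression to the mean alone.** Selecting on a single reading of at least 5, with SD 2, assumed population means of 5 to 7 and r = 0.5 to 0.8, gives a mean fall of 0.11 to 0.79 points and a significant pre-post test in about 5% to 46% of trials (17 or 20 women). The actual criterion covers at least 90% of attempts and a condition of at least 6 months, so the effect should be smaller than this.

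**6. Cost of the all-pairs family.** Six cells give 6 × 5 / 2 = 15 pairs. For a 2-point active-versus-sham difference with SD 2.0 and 17 per arm, the noncentrality is 2 / (2√(2/17)) = 2.92.

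- All-pairs Tukey: critical value 3.03 (32 df) to 2.94 (64 df), power about 0.47 to 0.50.
- Two contrasts, Bonferroni (α 0.025 each, 32 df): power about 0.71.

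At r = 0.5 the SD of change is also 2.0, so the 0.71 applies equally to differences in change from baseline.

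**The case against.** The strongest reply is that the plan already protects the efficacy claim. The main goal, the second expectation, the sample size and the interaction requirement are all between-arm. Efficacy needs the interaction as well as the contrasts, so if both arms fall equally the stated rule does not support a claim, and step 4 confirms this. That stands. A reader might infer that the efficacy test is invalid or has an inflated error rate; the document does not support that.

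A reader might also infer that the secondary objectives share the fault, because they mention the pretreatment assessment. They do not. They are worded as active versus sham, and the pretreatment reference can be read as defining change.

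Nor should regression to the mean be put first. The 90% and 6-month criteria select habitual pain rather than one high reading, and step 5 gives modest falls even without them. Sham response is the stronger driver.

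Finally, a contrast list is commonly left to the statistical analysis plan, which is not shown here. That is fair, and the absence of a list is not the point. The within-arm hypothesis is stated in the article itself, on the primary outcome, with significance predicted. The choice of an all-pairs method does nothing to set it aside.

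**Conclusion.** The point holds as a matter of what the trial may conclude. One of two expectations stated with equal standing can be met with no tDCS effect. For assumed non-specific falls of 1.0 to 2.0 points at r = 0.5, this would happen at one visit in about 49% to 97% of trials unadjusted, or 20% to 88% with Tukey. The size depends on the fall and the correlation, both assumed: at r = 0.3 a 1-point fall gives 37%, and at r = 0.5 a 0.5-point fall gives 16%. The logical point does not depend on either. The between-arm efficacy test remains valid. The all-pairs family also lowers power for the comparison of interest to about one half, against about 0.71 for two contrasts.

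**What to change.** - **Background:** make active versus sham the only confirmatory hypothesis. Delete the pre-post expectation or label it descriptive.
- **Statistical analyses:** limit the contrasts that support an efficacy claim to active versus sham in change from baseline at 2 weeks and at 3 months, with multiplicity control over those two (Bonferroni, for example).
- **Reporting:** give within-arm changes for both arms descriptively with confidence intervals, and state that they include sham response and regression to the mean.

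The secondary objectives need no rewording, and neither the sample size nor data collection changes. The small cost is that a within-arm fall can no longer be claimed as a confirmed hypothesis.

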### Randomization and blinding

After the pretreatment assessment, the participants are randomized into either the active or sham tDCS treatment (ratio 1:1) using permuted blocks of two and four. The allocation is managed by an individual independent from our research team who follows a computer-generated randomization list drawn up by an independent statistician. Participants, investigators, physiotherapist assessors, and the treatment provider remain blinded to group allocation and, therefore, cannot influence the process in any way.

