### Statistical considerations

#### Sample size, power, and statistical analysis methods

A total sample size of 34 participants is sufficient to detect a clinical minimal significant difference of 2 [67, 98] on an NRS (unpaired *t* test; α = 0.05; β = 0.80, standard deviation of 2.0) based on the efficacy of tDCS in other painful conditions [57, 99]. This estimation is conservative considering that tDCS in chronic pain demonstrated a mean pain reduction of 4.34 points [40] and that the available case study in a woman with vulvodynia showed a reduction of ten points [49]. To account for potential dropouts, a total of 40 subjects are being recruited. This estimated dropout rate (< 15 %) is based on available studies and our own RCT experience in women with PVD [13, 78, 100].

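### The hypothesis covers two visits, but no primary time point or success rule is fixed, and the sample size is tied to neither visit

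*Protocol article*

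**What the plan says.** All places are in the protocol article.

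- **Background.** The main between-group hypothesis is "We expect that active tDCS treatment will be more effective for reducing pain than the sham tDCS treatment at 2-week post-treatment and 3-month follow-up". Neither visit is ranked above the other.
- **Abstract and Primary outcome measure.** The primary outcome is pain during intercourse on a 0-10 scale: "participants are asked to evaluate their pain during intercourse with an NRS". Neither section says at which assessment it counts as primary.
- **Sample size, power, and statistical analysis methods.** "A total sample size of 34 participants is sufficient to detect a clinical minimal significant difference of 2", by an unpaired t test with "α = 0.05; β = 0.80, standard deviation of 2.0" (the 0.80 is evidently the power). No visit is named. The number is then raised: "To account for potential dropouts, a total of 40 subjects are being recruited".
- **Statistical analyses.** A mixed model has group and three times (baseline, 2 weeks, 3 months) as factors. Efficacy rests on a significant group-by-time interaction and on Tukey-Kramer contrasts. The section does not say which contrast decides.

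**The concern.** The hypothesis, primary outcome, sample size and decision rule are all stated in the article, and they do not point to the same test. The hypothesis names two visits, the sample size covers one comparison, and the decision rule is an omnibus test over three times.

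Two things are at stake. The first is what the 80% power refers to: it describes one comparison at one visit, and the reader cannot tell which. The second is what counts as a positive trial. Treatment lasts two weeks and the last assessment is three months after it, so the visits may disagree. If active treatment beats sham at one visit only, the plan has no rule for calling that success or failure.

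**Working it through.** **Inputs from the article.** Difference 2, SD 2.0, alpha 0.05, power 0.80, 34 evaluable, 40 recruited, dropout below 15%, 1:1 allocation.

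**Assumptions.** Tests are two-sided (not stated). The correlation rho between visits is not given and is taken as 0.3 to 0.7. The true effect is 2 points at both post-treatment visits unless stated otherwise.

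**1. The plan's own figure.** The standardised difference is 2/2 = 1. For n per arm the noncentrality is √(n/2) with 2n − 2 degrees of freedom. At n = 17 it is √8.5 = 2.92 on 32 df, and power is 80.7%. At n = 16 power is 78.1%. So 17 per arm, 34 in total, is right, and 34/0.85 = 40. The figure stands for one test at one visit.

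**2. Power across two visits.** Pairs of correlated two-sample t tests were simulated, each two-sided at 0.05 with no adjustment (200,000 runs per setting).

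| rho | Both visits, 34 evaluable | Both visits, 40 evaluable | At least one, 34 evaluable |
|---|---|---|---|
| 0.3 | 67.6% | 77.1% | 94.0% |
| 0.5 | 69.5% | 78.3% | 91.9% |
| 0.7 | 71.8% | 80.2% | 89.2% |

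Over the wider range rho 0 to 0.9, power for both visits is 65-76% with 34 and 76-83% with 40.

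The chance that exactly one visit is significant is the last column minus the first: 26.4%, 22.4% and 17.4% with 34 evaluable. Chance alone can therefore split the visits even when the effect is the same at both.

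**3. Size needed if both visits are required.** For 80% on the same tests: 44, 42 and 40 evaluable at rho 0.3, 0.5 and 0.7. Divided by 0.85 and rounded up, that is 52, 50 and 48 randomised, against 40 planned.

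**4. Does the interaction settle it?** Under compound symmetry its noncentrality is λ = n / [2σ²(1 − rho)] × Σ(δ_t − mean δ)², where δ_t is the group difference at each of the three times.

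- Sustained effect (0, 2, 2): the mean is 4/3 and the sum of squares is 16/9 + 4/9 + 4/9 = 8/3.
- Effect gone by 3 months (0, 2, 0): the mean is 2/3 and the sum of squares is 4/9 + 16/9 + 4/9 = 8/3.

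The sums are equal, so λ and the power are equal. At n = 17, σ² = 4 and rho 0.5, λ = 4.25 × 8/3 = 11.3 on 2 and 64 df, which gives about 85% power. At rho 0.3 and 0.7 it is about 70% and 97%. A significant interaction cannot tell the two patterns apart, so the contrasts must, and none is named as decisive.

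**The case against.** The strongest reply has four parts.

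- **The word *and* is not a success rule.** It appears in a statement of what the authors expect. The stated decision rule is in Statistical analyses and does not require both visits to win. This stands. The shortfall is therefore conditional on requiring both, and if either visit suffices on unadjusted tests, power exceeds 80%.
- **The planned analysis is not a raw t test.** The mixed model includes baseline. If the contrasts adjust for baseline (an assumption), power for both visits with 34 evaluable is about 70%, 82% and 95% at rho 0.3, 0.5 and 0.7. This also stands: from rho of about 0.5 the shortfall would disappear. The article does not use this to justify its sample size.
- **Type I error.** A reader might infer that two looks at 0.05 inflate the false-positive rate. Two free-standing unadjusted tests would give about 8-10%, but that is not the stated plan. The contrasts sit behind the interaction. Simulated under no effect, requiring a significant interaction and at least one significant visit gives about 1-2%, before any Tukey-Kramer adjustment. No inflation is claimed.
- **Detail may sit in an unseen analysis plan.** Test ordering often does. But the hypothesis, primary outcome, sample size and decision rule are printed here and do not fit together, so this part does not remove the point.

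A reader might also infer that a split result is likely, or that attrition is lowest at 2 weeks. The article supports neither. It argues for long-lasting effects and gives one overall dropout rate.

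**Conclusion.** The point holds as a mismatch between the parts of the plan, and it should be fixed. The sample-size arithmetic is sound, but its 80% describes a single comparison at a visit that is never named.

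Requiring both visits on unadjusted post-treatment t tests lowers power to about 67-72% with 34 evaluable and 77-80% with 40. This rests on a 2-point effect and SD 2 at both visits and on an assumed correlation of 0.3 to 0.7. A baseline-adjusted analysis could remove the shortfall at higher correlations, so its true size is unknown. It would be too strong to say that the trial is underpowered or that 34/40 is wrong: once one visit is named, those numbers stand.

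The part that depends on no correlation is the missing rule. Under compound symmetry the interaction responds equally to a lasting and a vanished effect, and nothing says which contrast decides, so a split result could be read either way after the fact.

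**What to change.** Before unblinding:

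1. Name one primary time point in Background and in Primary outcome measure. The 2-week post-treatment assessment is one reasonable choice; naming the 3-month visit would cure the fault equally.
2. In Statistical analyses, make the between-group contrast at that visit, from the planned mixed model, the deciding test at 0.05. Report the interaction as supportive. State that this single contrast carries no Tukey-Kramer adjustment, since the sample size allowed for none.
3. Make the other visit the key secondary comparison, tested at 0.05 only if the deciding test is significant.
4. Tie the 34/40 calculation to the named visit, and print 0.80 as power rather than β.

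Alternatively, state that superiority at both visits is required, and restate the power with the assumed correlation and the analysis used.

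The recommended route costs a few sentences and no extra participants. Its downside is that the second comparison cannot be confirmatory if the deciding test fails. The alternative keeps both visits confirmatory, but may need more than 40 women or a justified gain from baseline adjustment.
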